### Methods in analysis to handle protocol non-adherence and any statistical methods to handle missing data {20c}

We will use an intent-to-treat approach to analyze all available data; all participants will be assessed at baseline prior to randomization, so for the missing data, we will use the methods of the last observation carried forward or baseline observation carried forward to fill up.

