### Eligibility criteria {10}

Participants aged 18 to 60 years whose back pain has persisted for at least 12 weeks and are interested in participating in the trial will be recruited. Table 1 lists the exclusion criteria and the rationale for each criterion. The main screening criteria will be included in the registration questionnaire. We will contact possible eligible participants by telephone or WeChat and invited them to the hospital for final inclusion. In addition, if the participant does not receive treatment at the beginning or does not provide feedback data, we will define it as a drop out.

**Table 1 Tab1:** Exclusion criteria

Exclusion criteria	Rationale
Low back pain has lasted < 3 months	Not NCLBP.
There were clear “red flag signs” (unilateral leg pain and numbness consistent with nerve distribution, musculoskeletal-originated pain, intermittent claudication, weight loss without an obvious cause, back pain at night, trauma, etc.)	Our interventions may not be effective.
The history of spinal surgery	Back problem is complicated by medical or medicolegal issues.
A score < 4 on Roland-Morris Low Back Pain and Disability Questionnaire (RMDQ)	Back pain too mild to detect improvement.
Patients who practice meditation regularly (weekly) in past 3 months	Possible bias due to current or recent interventions.
Patients who participated in courses related to core stability exercises in the past 3 months	Possible bias due to current or recent interventions.
Conditions that may be uncontrolled for self-compassion meditation (e.g., psychosis, major depression or anxiety, current self-harm, or suicidal ideation)	Condition would make it difficult to control or cause harm to participants.
Unable to independently complete Chinese language questionnaires	Condition would make it difficult to communicate.

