### Sample size {14}

Sample size calculation will be based on the results of our pilot study [34]. We found a mean difference of 5.5 for RMDQ with a standard deviation of 4.7 in the intervention group and a mean difference of 3.1 with a standard deviation of 4.8 in the control group at 16-week follow-up. To detect it at 16 weeks with a two-sided significance level (alpha) of 0.05 and a power of 80% with equal allocation to two arms, it would require 66 patients in each arm of the trial. To allow for 20% drop out, future study must include at least 166 participants (83 in each group). The calculation was performed with the PASS software(version 15).

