### Recruitment {15}

Participants will be recruited in eight waves of 20 participants each. Recruitment will be advertised in notices posted in the clinic and on a social network platform (WeChat). The main inclusion and exclusion criteria will be included in our registration questionnaire. Possible eligible participants will be invited to come to the hospital for a physical examination and baseline assessment. Eligible participants will be assigned a number according to the sequence of their arrival at the hospital and a to the research assistant ([name]) for random grouping. Participants will be informed of the time of treatment after baseline assessment, so that the participants could arrange the time. Treatment content will be announced 3 days before the start of the intervention.

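### Carry-forward is the only stated method for missing outcomes: baseline carry-forward dilutes the 16-week difference at the planned 20% dropout and biases it if dropout differs by arm

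*Protocol article*

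**What the plan says.** The section on non-adherence and missing data {20c} commits to intention to treat on all available data. It notes that everyone has a baseline assessment, and then says "we will use the methods of the last observation carried forward or baseline observation carried forward to fill up". No rule says when each of the two applies, and no other missing-data method appears in the article.

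Three other places bear on this:

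- Eligibility criteria {10}: for a participant who "does not receive treatment at the beginning or does not provide feedback data, we will define it as a drop out".
- Sample size {14}: the pilot gave a "mean difference of 5.5 for RMDQ with a standard deviation of 4.7 in the intervention group"; the control arm changed by 3.1 points (SD 4.8). From this, "it would require 66 patients in each arm of the trial", and then "To allow for 20% drop out, future study must include at least 166 participants", 83 per arm.
- Recruitment {15}: "Treatment content will be announced 3 days before the start of the intervention".

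Outcomes are measured at baseline, week 4 and week 16, and week 16 is the primary end point. Week 4 is therefore the only post-baseline value that LOCF can carry to the primary time point.

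**The concern.** Carry-forward puts a fixed value where the 16-week outcome is unknown and then analyses it as if it had been measured. In this trial both arms are expected to improve, so a carried baseline is a claim of no improvement. Each arm's mean change then shrinks in proportion to its own dropout rate. With equal rates the difference is diluted. With unequal rates a difference can appear where there is none, or a real one can be masked.

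The sample size and the analysis also describe different quantities. The inflation from 66 to 83 treats dropouts as contributing nothing, with the full 2.4-point difference kept among the 66 who remain. The analysis instead keeps all 83 per arm, with filled values among them.

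Arm-dependent dropout is possible. Participants learn the treatment content shortly before the start, those who never start count as dropouts, and the combined arm carries an extra two hours of training before each exercise session.

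**Working it through.** **Inputs.** From Sample size {14}: changes 5.5 (SD 4.7) and 3.1 (SD 4.8), hence a difference of 2.4 and pooled SD √((4.7² + 4.8²)/2) = 4.75; "two-sided significance level (alpha) of 0.05 and a power of 80% with equal allocation to two arms"; 66 evaluable per arm; 20% dropout; 83 enrolled per arm. Dropout is taken as unrelated to outcome. The test is approximated by a two-sided comparison of mean changes at week 16, which is the comparison the sample size describes.

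**The plan's own figures.** Per arm, n = 2 × (4.75 × (1.96 + 0.84)/2.4)² ≈ 61.5, so 62, or 63 with the exact t-test. The stated 66 is slightly conservative. The inflation reproduces: 66/0.8 = 82.5, so 83 per arm and 166 in total. With 66 observed per arm, SE = 4.75 × √(2/66) = 0.827 and z = 2.4/0.827 = 2.90. Power is 82.7% (normal) or 82.1% (t).

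**BOCF, 20% dropout in each arm.** With dropout p, mean change m and SD s, the filled data have mean (1 − p)m and variance (1 − p)s² + p(1 − p)m².

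- Combined arm: mean 0.8 × 5.5 = 4.40; variance 0.8 × 22.09 + 0.16 × 30.25 = 22.51.
- Control arm: mean 0.8 × 3.1 = 2.48; variance 0.8 × 23.04 + 0.16 × 9.61 = 19.97.
- Difference 1.92; SE √((22.51 + 19.97)/83) = 0.715; z = 2.68; power 76.5% (76.3% in a 40,000-run t-test simulation).
- About 91 per arm would be needed for 80% under this rule.

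**LOCF from week 4.** The article gives no week-4 result. Assume that carried values have the week-16 SDs and that the control arm's week-4 change is between half and all of 3.1.

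| Week-4 difference, as share of 2.4 | Power |
|---|---|
| 0% | 71–73% |
| 25% | 77–79% |
| 50% | 82–83% |
| 75% | 86–87% |
| 100% | about 90% |

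Power is below 80% only when the week-4 difference is less than roughly one third to one half of the 16-week difference.

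**Mixture of the two.** If the week-4 effect equals the week-16 effect, power is 90, 84, 80.5 and 76.5% when 0, 50, 75 and 100% of dropouts have only a baseline value.

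**Uncertainty.** The SE is 0.715 under BOCF, and 0.737 under LOCF when week-4 changes match week 16. The 66 per arm actually observed support 0.827. The ratios 0.715/0.827 and 0.737/0.827 are shortfalls of about 14% and 11% for the true 16-week difference.

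**Equal dropout, no true effect, BOCF.** Simulated rejection is 4.9%.

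**Unequal dropout, BOCF.** The splits are assumptions, each averaging 20%. With no true effect and both arms improving by 3.1, the false difference is 3.1 times the gap in dropout:

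| Dropout split | False difference | SE | Rejection |
|---|---|---|---|
| 17.5% vs 22.5% | 0.155 | 0.687 | 5.6% |
| 15% vs 25% | 0.31 | 0.686 | 7.4% |
| 10% vs 30% | 0.62 | 0.685 | 14.8% |

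With a true difference of 2.4 and a 10%/30% split:

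- Control arm loses more: 0.9 × 5.5 − 0.7 × 3.1 = 2.78.
- Combined arm loses more: 0.7 × 5.5 − 0.9 × 3.1 = 1.06, power 31%.

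**The case against.** **LOCF need not cost power.** A reader might infer that either form of carry-forward takes power below 80%. The document does not support that. The 76.5% needs every dropout to contribute baseline only. If the week-4 difference is about half or more of the 16-week one, LOCF stays above 80%. This objection stands, and the power loss is limited to BOCF and to LOCF where no week-4 value exists.

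**Dropout may not differ by arm.** No rates by arm are given. The announcement of content and the definition of dropout apply to both arms alike. Both arms pay a refundable deposit, with 80 of 100 yuan tied to the second follow-up visit, and questionnaires are completed by QR code. These features favour retention, so unequal dropout is a risk and not a prediction. The larger error rates depend on the wider assumed splits.

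**The rule may be less open than it looks.** One could read the wording as leaving the choice until the data are seen. It can equally mean week 4 if present, otherwise baseline, which follows naturally from the remark that everyone has a baseline. The wording is ambiguous, and nothing says the choice is made late.

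**No general false-positive inflation.** With equal dropout the type I error stays nominal, and the understated SE shows as false precision about a diluted estimate.

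**Non-starters are not excluded.** They are labelled dropouts, but the intention-to-treat commitment keeps them.

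None of this defends carry-forward as the only stated method.

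**Conclusion.** The point holds in limited form. The one missing-data method that the article states attaches a specific and unlikely value to the primary outcome of dropouts.

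Under BOCF, or LOCF where only baseline exists, 20% dropout in both arms cuts the expected difference by a fifth, to 1.92, and power to about 76.5%, against about 82% for the 66 observed per arm that the sample size relies on. LOCF from week 4 lies anywhere from about 71 to 90%, under the assumptions stated for week 4. The SE is about 11 to 14% too small for the true 16-week difference. Bias in either direction follows if dropout differs by arm, and its size depends on splits that the document does not give.

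It would be wrong to infer that 166 participants are too few. Without carry-forward, and with data missing at random, that number keeps about 82% power. The weakness lies in the analysis rule.

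**What to change.** In {20c}, replace carry-forward as the primary method with one of two options:

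- a likelihood-based mixed model for repeated measures with baseline, week 4 and week 16 all in the outcome vector and baseline means constrained equal between arms; or
- multiple imputation.

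Baseline has to be in the outcome vector. A model on week-4 and week-16 values alone would drop anyone with no post-baseline measurement, which conflicts with keeping everyone randomised, non-starters included. The repeated-measures ANOVA in {20a} should be reworded to match.

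Add a delta-adjusted or reference-based multiple-imputation sensitivity analysis. LOCF or BOCF may stay as a labelled sensitivity analysis, with the rule for which applies fixed in advance.

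The cost is a change of wording and a little more analysis work; the sample size need not change. The primary model would rest on missing at random, which the added sensitivity analysis tests.

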### Plans to give access to the full protocol, participant-level data, and statistical code {31c}

According to the data sharing statement, we will deliver a completely deidentified data set to an appropriate data archive for sharing purposes no later than 3 years after the collection of the 1-year post-randomization interviews.

#### Composition of the data monitoring committee, its role, and reporting structure {21a}

A Data Monitoring Committee (DMC) is not needed, because our trial is of short duration and with known minimal risks. But the researchers ([name] and [name]) will regularly analyze the data to make adjustments.

#### Adverse event reporting and harms {22}

In this study, physical discomfort due to exercise will be defined as an adverse event. In the treatment process, the participants will be asked to fill in a training diary every day to report their physical conditions, so as to detect adverse events and deal with them in a timely manner.

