### Trial design {8}

The trial was designed as a randomized, controlled, observer- and patient-blinded trial with two parallel groups. Randomization will be performed as block randomization with a 1:1 allocation. The control group will receive CSE only while the intervention combined group will receive a combination of CSE and SCT. Participants will be asked to complete a follow-up assessment at weeks 4 (post-treatment) and 16 (primary end point) after randomization (Fig. 1).

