#### Core stability exercise (CSE)

The face-to-face group core stabilization training of 1.5 h will be conducted under the supervision and guidance of professional physiotherapists on weekends. After the training, homework will be arranged for the subjects using the AUK Sports Training System. The participants will be asked to complete at least three home-based training sessions per week with a training time of 20 to 30 min [22] and to complete the daily training diary after training. The overall training lasted for 4 weeks. The first week will be spent mainly teaching the participants stretching exercises. In the second week, low-difficulty strength training will be added on top of the stretching training. In the third week, the participants will be taught more difficult strength training. In the last week, according to the actual condition of the participants, a set of exercise programs suitable for them will be determined (see Table 2 and Fig. 3). The program will be led by two professional physiotherapists with at least 5 years of experience ([name] and [name]).

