#### Criteria for discontinuing or modifying allocated interventions {11b}

Excessive exercise or inadequate warm-up will cause muscle pain (NRS > 7). In the event this happens, the participant should be told to reduce the intensity of the exercise or to rest for a few days.

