### Intervention-related information

Intervention-related information will be evaluated by class attendance, adverse events, and exercise adherence. Class attendance will be assessed by class records. Exercise adherence and adverse events will be recorded using the home practice diary.

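### The adverse event definition covers only bodily discomfort from exercise, which both arms receive, so direct psychological harm from self-compassion training and unrelated medical events are not recorded as adverse events

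*Protocol article*

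**What the plan says.** The section on adverse event reporting and harms {22} gives the only definition in the document: "In this study, physical discomfort due to exercise will be defined as an adverse event". Detection follows the same line: "the participants will be asked to fill in a training diary every day to report their physical conditions". The section on intervention-related information names the source: "Exercise adherence and adverse events will be recorded using the home practice diary". The CSE section asks participants "to complete the daily training diary after training".

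On the difference between the arms, the trial design section says: "The control group will receive CSE only while the intervention combined group will receive a combination of CSE and SCT".

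Table 1 (exclusion criteria) excludes people with psychosis, major depression or anxiety, current self-harm or suicidal ideation, and links these conditions to self-compassion meditation. The reason given is: "Condition would make it difficult to control or cause harm to participants".

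The data monitoring section explains the absence of a committee partly by saying that "our trial is of short duration and with known minimal risks".

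**The concern.** The definition sets two conditions: the event must be physical, and it must be caused by exercise. Distress or worsening mood brought on by an SCT session meets neither. A medical event with another cause fails the second. However well the diary is kept, such events are not adverse events under the stated rule.

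This matters because SCT is what the trial adds. The adverse event record would describe the component common to both arms and be silent on direct harm from the component that differs. With no monitoring committee, that record is the main place where individual harms would appear. An analysis plan cannot repair this later, because it can tabulate only what was collected.

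**Working it through.** The point concerns a definition. The plan has no figure to reproduce, so the check is a side-by-side reading followed by a labelled illustration.

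**1. Is the definition widened anywhere?**
- Intervention-related information: lists adverse events and their source, with no definition.
- Table 3: schedules adverse events during weeks 1–4 and at weeks 4 and 16, with no definition.
- Criteria for discontinuing or modifying interventions {11b}: "Excessive exercise or inadequate warm-up will cause muscle pain (NRS > 7" and what follows concern exercise only.
- Auditing {23}: covers the reporting of harms but does not redefine them.

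The harms section therefore stands alone.

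**2. Which component does it cover?**

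| Component | Combined arm | Control arm | Can produce a defined adverse event directly? |
|---|---|---|---|
| CSE | yes | yes | yes, if physical |
| SCT | yes | no | no |

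The abstract gives 2 hours of SCT before CSE and Table 2 lists four SCT sessions, so exposure is about 4 × 2 = 8 hours plus home practice, all in one arm.

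**3. Does the source allow for more than the definition?** No. The harms section describes a daily diary and the CSE section a diary completed after training. On either reading it is a training diary, and the harms section directs it at physical condition.

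**4. What else captures psychological change?** GAD-7, PHQ-9 and SF-36 are measured in both arms at baseline, week 4 and week 16 as secondary outcomes. The article gives them no harm threshold and no link to adverse event reporting.

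**5. Illustration.** The 83 per arm comes from the sample size section, and 66 is the number there before the 20% dropout allowance. The event rates p are assumptions; the document gives none.

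Expected events = 83 × p. Chance of at least one event = 1 − (1 − p)^n.

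| Assumed p | Expected, n = 83 | At least one, n = 83 | At least one, n = 66 | Counted as adverse events |
|---|---|---|---|---|
| 1% | 0.83 | 57% | 48% | 0 |
| 2% | 1.66 | 81% | 74% | 0 |
| 5% | 4.15 | 98.6% | 96.6% | 0 |
| 10% | 8.3 | 99.98% | 99.9% | 0 |

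For example, at 2%: 1 − 0.98^83 = 0.813. The last column is zero by definition, because these events are neither physical nor due to exercise.

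**The case against.** The strongest reply is that psychological deterioration is measured, with validated scales and a concurrent control arm. That stands in part. A reader might infer that the trial cannot see any harm from SCT, and the documents do not support this. Mean worsening in anxiety, depression or the mental component of SF-36 would show by arm. Hypothesis 1 also expects SCT to raise exercise adherence, so extra exercise discomfort arising in that way would count as an adverse event. What remains uncounted is direct, individual harm: transient distress between visits, a serious psychological event in one person, or a medical event not due to exercise.

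A second reply is that the risk is reduced by the exclusions in Table 1 and by the supervising counselling psychologist. That may lower the rate, but it does not record what still occurs.

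A third is that neither stated aim concerns safety and no between-arm test of harms is planned. That is correct. A reader might go on to infer a planned claim that no SCT events occurred in 83 participants, and attach a confidence limit to it. The protocol proposes no such report.

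A reader might also infer that unblinded people judge whether an event is due to exercise, so that counts would drift by arm. No section says who assigns cause. The trial design section calls the trial patient- and observer-blinded, while the blinding section says that therapists are not blinded. Arm-dependent attribution is possible but not shown.

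Finally, an article condenses a fuller protocol. Here, however, the definition is stated, not left out. If a fuller document holds a wider one, the article contradicts it.

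**Conclusion.** The point holds in a limited form. The stated definition omits direct psychological harm from SCT, and medical events unrelated to exercise, from the adverse event record, although Table 1 recognises that self-compassion meditation may cause harm. Mean psychological worsening by arm remains visible through the secondary outcomes. The primary and secondary efficacy inference is unaffected.

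The number of events missed cannot be derived from the document. The illustration shows only that, at assumed rates of 2% or more and 83 participants, at least one uncounted event would be likely. It rests on those rates, on independence between participants, and on full observation; the 66-participant column shows that losing the allowed dropout changes little.

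This should be corrected, because any later statement about the safety of adding SCT would otherwise lack individual event data on SCT.

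**What to change.** Replace the definition in the harms section with wording to this effect: an adverse event is any new or worsened physical or psychological symptom, or any medical event, from randomisation to week 16, in either arm and whatever the presumed cause.

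Then align collection and reporting:
- Ask the same question in both arms, from a source that does not depend on having exercised. An item on the existing electronic questionnaire at weeks 4 and 16, as well as on the daily form, would do; Table 3 already schedules adverse events at those weeks. Changing the definition alone, or adding a field to the training diary, would not be enough, because that diary is tied to exercise and physical condition.
- Record presumed relation (exercise, SCT, neither) as a separate descriptive field. Relation to SCT cannot apply in the control arm, so counts by relation are not comparable between arms.
- Compare all-cause event counts and numbers of participants affected by arm.

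The cost is an amendment by the route the protocol already describes (ethics committee approval first), a short questionnaire item, and more minor events to tabulate. The trial status section gives April 15, 2021 as the first day of recruitment, so the change would split the record: events must be reported separately for recruitment waves before and after the amendment. No treatment or management rule changes.

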#### Intervention description {11a}

We will randomize participants with NCLBP into two groups: the intervention combined group (ICG) will receive m-health-based SCT plus CSE (the same day), and the control group (CG) will receive m-health-based CSE only. The treatment will be divided into two parts: face-to-face intervention and self-help exercise at home. The face-to-face intervention will take place in the Rehabilitation Clinic of the First Affiliated Hospital of Sun Yat-Sen University on Saturday or Sunday for 4 weeks in total, because most NCLBP patients need to work on the weekdays. The self-help exercise was provided by the Anyoukang (AUK) exercise training system, which would provide daily exercise reminders and video guidance via WeChat (Fig. 2).

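### The adverse event definition covers only physical discomfort from exercise, which both arms receive, so psychological and other non-exercise events fall outside the count although SCT is what is randomised

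*Protocol article*

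**What the plan says.** The section on adverse event reporting and harms {22} gives the article's only definition: "physical discomfort due to exercise will be defined as an adverse event". For detection, the same section has participants "fill in a training diary every day to report their physical conditions, so as to detect adverse events".

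The section on intervention-related information names the source: "Exercise adherence and adverse events will be recorded using the home practice diary". The CSE section introduces the diary as homework and asks participants "to complete the daily training diary after training". The adherence section {11c} likewise places it after exercise.

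The intervention description {11a} sets out the contrast: "the intervention combined group (ICG) will receive m-health-based SCT plus CSE (the same day", whereas "the control group (CG) will receive m-health-based CSE only".

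Table 1, under eligibility criteria {10}, excludes "Conditions that may be uncontrolled for self-compassion meditation (e.g., psychosis, major depression or anxiety, current self-harm, or suicidal ideation". The rationale given is "Condition would make it difficult to control or cause harm to participants".

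Table 3 lists adverse events in weeks 1–4, at week 4 and at week 16. It also lists PHQ-9, GAD-7 and SF-36 at baseline, week 4 and week 16, all as secondary outcomes.

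**The concern.** The definition restricts events in two ways: by nature (physical) and by cause (exercise). Exercise is common to both arms, and the randomised difference is a psychological intervention. The events most specific to that intervention, such as distress or lowered mood during a meditation practice, meet neither condition.

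This sits badly with Table 1, which recognises a possibility of harm in connection with self-compassion meditation when it screens people out. Nothing in the adverse event definition corresponds to that possibility once treatment begins.

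What is at stake is the safety statement the trial can make, not the efficacy result. The section on the data monitoring committee {21a} dispenses with a committee partly because the risks are regarded as known and minimal. For SCT, adverse event data collected under this definition cannot test that premise.

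**Working it through.** The article states no adverse event rate, so there is no figure to reproduce. The check is mainly textual.

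**Step 1: does any section widen the definition?**

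| Section | Content | Widens it? |
|---|---|---|
| Harms {22} | Physical discomfort caused by exercise; diary asks about physical condition | No, this is the definition |
| Intervention-related information | Diary is the source for adherence and adverse events | No |
| Criteria for discontinuing or modifying {11b} | Concerns exercise-related muscle pain | No |
| Table 3 | Schedules adverse events at three time points | No, timing only |
| Auditing {23} | Reporting of harms is among the processes that may be reviewed | No |
| PHQ-9, GAD-7, SF-36 | Secondary outcomes in both arms | No rule turns a worsening into an adverse event |

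**Step 2: classify three kinds of event under the definition as written.**
- Muscle pain after a CSE session, either arm: counted.
- Distress during an SCT session, combined arm: neither physical nor caused by exercise, so not counted.
- A physical event not attributed to exercise, either arm: not counted.

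**Step 3: what the questionnaires recover.** The statistical methods section {20a} analyses continuous secondary outcomes by repeated-measures ANOVA. That compares group means at fixed times. An average improvement can hide a few individuals who deteriorate, and an episode that arises and resolves between assessments may not appear at all.

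**Step 4: size, for illustration only.** Inputs: N = 83 in the combined arm (abstract and sample size section {14}), and an assumed rate p of psychological events attributable to SCT. Expected number = N × p; chance of at least one = 1 − (1 − p)^N.

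| Assumed p | Expected among 83 | Chance of at least one | Counted as adverse events |
|---|---|---|---|
| 1% | 83 × 0.01 = 0.83 | 57% | 0 |
| 5% | 83 × 0.05 = 4.15 | 98.6% | 0 |
| 10% | 83 × 0.10 = 8.3 | above 99.9% | 0 |

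**Step 5: what a zero count would mean.** If psychological events were fully recorded and none occurred among n participants, the exact one-sided 95% upper bound for the rate would be 1 − 0.05^(1/n).
- n = 83: 1 − 0.05^(1/83) = 3.5%.
- n = 66, the article's number per arm before its 20% dropout allowance: 1 − 0.05^(1/66) = 4.4%.

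Under the current definition the count of such events is zero whatever the true rate, so neither bound applies.

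**Step 6: the diary.** The harms section says every day; the CSE and adherence sections say after training or exercise. If completion in practice follows exercise, someone who stops exercising may also stop reporting. Hypothesis 1 (Objectives {7}) expects SCT to raise CSE adherence, so the chance of recording an event could then differ between arms.

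**The case against.** The strongest reply is that psychological harm is not invisible. PHQ-9, GAD-7, the SF-36 with its mental component, and pain catastrophizing are all measured in both arms at baseline, week 4 and week 16, and a counseling psychologist supervises the SCT sessions. This stands. A reader might infer that every SCT-related harm would be missed; the article does not support that. What it supports is narrower: such harm is not classified as an adverse event, and acute distress between assessments has no stated adverse event route.

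Second, a reader might infer from the diary wording that adverse event counts are not comparable between arms. That is not shown. The harms section asks for daily completion, the adherence section adds daily electronic reminders, and Table 3 schedules adverse events at weeks 4 and 16. Dependence of recording on adherence is a risk and a lesser point.

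Third, exercise discomfort is not irrelevant to SCT. If SCT raises adherence, more exercise discomfort is a plausible downstream effect, and a difference between arms would be informative. This also stands, but it concerns only the exercise pathway.

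Fourth, Table 1 should not be read as saying that self-compassion meditation harms patients. The subject of its rationale is the condition, the wording is ambiguous, and the exclusion removes those of most concern. It shows only that the possibility of harm was considered.

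Fifth, a journal article leaves operational detail to the full protocol, and this one states no between-arm adverse event test. That would excuse a missing procedure. Here a definition is stated, and the objection is to its content.

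**Conclusion.** The point holds in limited form. As written, the adverse event definition excludes psychological events and any event not attributed to exercise, and nothing else in the article widens it. An adverse event count of zero would therefore neither support a safety statement about SCT nor confirm the minimal-risk premise used to forgo a monitoring committee.

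The size cannot be taken from the document. The figures of about 1, 4 and 8 uncounted participants out of 83 rest on assumed rates of 1%, 5% and 10%; the conclusion depends on none of them. It rests on reading the stated definition as the operative one, since no other appears. The primary efficacy analysis is unaffected. This should be changed, but it does not threaten the main result.

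**What to change.** 1. Define an adverse event as any new or worsening physical or psychological event in either arm, whatever its presumed cause. Record attribution (exercise, SCT, other, unknown) in a separate field.
2. Ask the same fixed question of every participant in both arms at the weekly sessions and at the week-4 and week-16 points already in Table 3. Keep this independent of the exercise diary, so that reporting does not depend on having trained.
3. Tabulate by arm the number of participants whose PHQ-9 or GAD-7 worsened from baseline, using data already planned, with the threshold for worsening fixed before the data are examined.
4. Reconcile the statements on whether the diary is completed daily or after exercise.

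The cost is an amended definition, one questionnaire item and a larger number of reported events, many probably unrelated to treatment. No extra visit is needed, and no dose, schedule or treatment rule changes.
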